# Effect of Greenshell^TM^ mussel on osteoarthritis biomarkers and inflammation in healthy postmenopausal women: a study protocol for a randomized double-blind placebo-controlled trial

**DOI:** 10.1186/s13063-021-05473-5

**Published:** 2021-07-28

**Keywords:** Osteoarthritis, Biomarker, Inflammation, Greenshell mussel, Green-lipped mussel

## Abstract

**Background:**

New Zealand Greenshell™ mussels (GSM; *Perna canaliculus*) have recently been shown to decrease cartilage degradation in a rat model of induced metabolic osteoarthritis (MetOA). However, this effect has not been investigated in human subjects. This study aims to determine the effect of GSM powder on biomarkers of cartilage metabolism, bone resorption, and inflammation in New Zealand healthy overweight/obese postmenopausal women who are at early stage or at high risk of OA.

**Method:**

Fifty overweight or obese (BMI 25–35 kg/m^2^) postmenopausal women (aged 55–75 years) will be recruited by advertisement. Participants will be randomized based on a double-blind randomization schedule and stratified randomization based on BMI and age distribution. The participant will be assigned with a 1:1 allocation ratio to receive 3 g/d whole meat GSM powder or placebo (sunflower seed protein) for 12 weeks. Data on socio-demographics, physical activity, and dietary intake will be collected for each subject. Cartilage turnover biomarkers [(C-telopeptide of type II collagen (CTX-II), C-propeptide of type II procollagen (CPII), Cartilage oligomeric matrix protein (COMP)], and bone resorption marker (CTX-I) will be measured in blood and urine samples. Inflammatory status (hs-CRP and cytokine panel) will be assessed and iron status will be measured. Body composition including fat mass (FM), lean mass (LM), and fat percentage will be measured using dual-energy X-ray absorptiometry (DXA). Joint pain and knee function will be assessed using a 100-mm visual analog scale (VAS) and the Knee Injury and Osteoarthritis Outcome Score (KOOS) questionnaire, respectively.

**Discussion:**

This trial will be the first to explore the effects of whole meat GSM powder on cartilage turnover, bone resorption, and inflammation biomarkers in overweight/obese postmenopausal women. The results from this trial will provide evidence on the efficacy of GSM in the prevention of OA.

**Trial registration:**

Australian New Zealand Clinical Trials Registry (ANZCTR) ACTRN12620000413921p. Registration on 27 March 2020.

## Background

Osteoarthritis (OA) is the most common type of degenerative joint disease, contributing to progressive pain and functional loss. It is estimated to affect 33.6% of the elderly over 65 years of age [1, 2]. OA affects an estimated 3.7% of the population worldwide and that equates to approximately 268 million people [3]. The public health burden of OA is increasing, in parallel with aging and obesity. OA is more prevalent in women compared to men, and the incidence is accelerated following menopause [4]. Estrogen depletion is an important risk factor for OA, possibly due to the presence of estrogen receptors (ERs) in joint tissues [5].

Menopausal transition is accompanied by weight gain which contributes to several health risks including musculoskeletal diseases [6]. An increased body mass index (BMI) is strongly related to an increased risk of knee and hip OA [7]. Excess body weight not only increases the OA risk at weight-bearing joints due to increased mechanical loading; it has been shown to increase the risk of OA in non-weight-bearing joints such as in the hands [8]. Increased adipose tissue secretes adipokines and pro-inflammatory cytokines contributing to low-grade systemic inflammation [9]. Tumor necrosis factor-alpha (TNF-α), interleukin-1 beta (IL-1β), and interleukin-6 (IL-6) play a crucial role in cartilage loss and bone resorption in the pathogenesis of OA. These cytokines induce the production of cartilage degrading enzymes and suppress the synthesis of collagen type II and other cartilage matrix components [10].

So far, no therapeutic strategies have been proven yet and conventional treatments, particularly non-steroidal anti-inflammatory drugs (NSAIDs), have been used to reduce inflammation and symptoms. Prolonged use of NSAIDs has been associated with adverse side effects such as gastric or peptic ulcers [11]. Hence, the identification of safe interventions for disease prevention and treatment of early OA has become increasingly important. Green-lipped mussels (*Perna canaliculus*) or Greenshell™ mussels (GSM) is a known commercial aqua cultured species native to New Zealand (NZ). GSM contains high amounts of long-chain omega-3 polyunsaturated fatty acids (n-3 PUFA), eicosapentaenoic acid (20:5 n-3 EPA) and docosahexaenoic (22:6 n-3 DHA), and several other bioactive compounds [12]. With potent anti-inflammatory properties, GSM oil extracts have been shown to alleviate the arthritic symptoms [13].

The chondroprotective effect of GSM has recently been reported in an experimental model of OA. In this study, serum concentration of the cartilage degradation biomarker C-terminal telopeptides of type II collagen (CTX-II) was significantly reduced after GSM powder was added to the diet of rats actively developing metabolic OA [14]. Results from this preliminary study support the potential for an intervention study supplementing human subjects with GSM powder in order to slow the development of OA.

Obesity predisposes individuals to subclinical inflammation and concurrently reduces iron absorption and systemic iron availability from cellular iron stores [15]. Obese people are at risk of developing iron deficiency, leading to escalation of the disease burden [16]. GSM contains a high concentration of both haem and non-haem iron as well as iron absorption enhancers including myofibrillar proteins, low-molecular-weight aminoglycans, and n-3 PUFA [17]. GSM enhanced the non-haem iron uptake in human intestinal epithelial cells (Caco-2) to a similar extent to that of beef [18]. For these reasons, we hypothesize that GSM could potentially improve the iron status biomarker.

To date, there has been no previous trial investigating the effect of GSM powder on OA biomarkers in human subjects. Therefore, the current clinical trial aims to investigate the effect of powder derived from New Zealand GSM on biomarkers of cartilage turnover, inflammation, body composition, and outcomes of joint pain and knee function in healthy overweight or obese postmenopausal women who are at great risk of developing OA.

## Methods

### Study design

This is a randomized, double-blind, placebo-controlled trial. The flowchart of the study protocol is illustrated in Fig. 1. This study will be conducted at Human Nutrition Research Unit at Massey University, Palmerston North, New Zealand.

**Fig. 1 Fig1:**
[figure not shown]
Flowchart describing the study

### Sample size

The sample size calculation applies to CTX-II/creatinine, CTX-II/procollagen II C-propeptide (PIICP) also referred as (CPII) CPII ratio, and cartilage oligomeric matrix protein (COMP) as the primary outcome variables. For CTX-II/ creatinine as well as CTX-II/ CPII a sample size of 24 is required to detect a 20% relative difference from baseline with 80% power. Hence, 25 subjects will be recruited for each group (GSM and placebo). For COMP as well as CPII a sample size of 7 is required to detect a 20% difference from baseline. This randomized double-blind placebo-controlled trial in parallel design recruit 55 (allowing for 10% potential dropout rate, with 27–28 sample in each arm).

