### Statistical analysis

Statistical analysis will be performed using IBM statistics software version 25 (Armonk, NY, USA). The values of variables will be presented as mean ± standard deviation. Normality tests will be assessed through Shapiro-Wilk tests carried out on each parameter before analysis. Analysis includes all the participants (intent to treat) determining the baseline characteristic. Additional analysis will be performed per protocol on participants with 80% or higher adherence to study protocol. Two-way repeated measures ANOVA will be used to determine differences within groups (pre vs. post) as a repeated factor and intervention (GSM vs. placebo) as a fixed factor, with the model adjusted for the BMI and age, physical activity, and baseline vitamin D status. Post hoc analysis with Bonferroni adjustments will be performed for multiple comparisons. Statistical significance will be set at a level of 0.05.

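### The trial is sized on a 20% change from baseline, and that n is then used per arm, so 80% power for GSM versus placebo on the two CTX-II ratios is not established

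*Protocol article*

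**What the plan says.** The Sample size section gives one effect size for the two CTX-II ratios: "a sample size of 24 is required to detect a 20% relative difference from baseline with 80% power". The next sentence turns that number into an arm size: "Hence, 25 subjects will be recruited for each group (GSM and placebo". The same form of words is used for the other markers: "For COMP as well as CPII a sample size of 7 is required to detect a 20% difference from baseline". The section ends by describing a parallel design with 55 recruited, "allowing for 10% potential dropout rate".

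The comparison that the design sets up is between arms. The abstract has participants "assigned with a 1:1 allocation ratio to receive 3 g/d whole meat GSM powder or placebo", and the Statistical analysis section enters intervention as the between-group factor in a repeated measures ANOVA. That section also sets the level: "Statistical significance will be set at a level of 0.05". The Primary outcomes section, like the Sample size section, words its contrast as end of study against week 6 and baseline, and does not name GSM versus placebo.

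**The concern.** A change from baseline is a one-group, paired quantity. The difference between two independent arms in that change has twice the variance that one arm's mean change has at the same n. A number that gives 80% power for the first does not give 80% power for the second if it is simply used again as the size of each arm.

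The CTX-II ratios matter most here. They need the larger n (24 against 7) and so fix the size of the trial, and CTX-II is the marker behind the preclinical rationale in the Background and Discussion. If the power for them is overstated, a null GSM-versus-placebo result would be read as 80%-powered evidence against a 20% effect when the chance of detecting such an effect may have been near even.

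**Working it through.** **Inputs from the protocol article.** Effect 20%, described relative to baseline; power 80%; n = 24 for the CTX-II ratios and n = 7 for COMP and CPII; 25 per arm; 1:1 allocation (all from Sample size and the abstract); level 0.05 (Statistical analysis).

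**Assumptions.** Two-sided test, since sidedness is not stated; 80% power for n = 7 as well, since it is not restated there; placebo arm unchanged on average; equal SD in both arms.

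**Reproducing the stated figure.** With no SD, CV or correlation given, n = 24 cannot be reproduced directly. The SD that it implies can be solved for under each reading, using the noncentral t distribution.

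*Reading A: paired, as worded.* The noncentrality is d × √n, with n − 1 degrees of freedom.
- n = 24 and 80% power give d = 0.597.
- Implied SD of change = 20 / 0.597 = 33.5% of baseline.

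Between arms, the noncentrality is d × √(n/2), with 2n − 2 degrees of freedom.
- At 25 per arm: 0.597 × √12.5 = 2.11 on 48 degrees of freedom, so power is 54%.
- At 27 per arm, with almost no dropout: 58%.
- Detectable at 80% power with 25 per arm: d = 0.809, and 0.809 × 33.5% = 27%.
- Per-arm n for 80% power at a 20% difference: 45.

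The normal approximation gives nearly the same picture: SD 35.0%, power 52% at 25 per arm, and 48 per arm for 80%.

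*Reading A with adjustment for the baseline value.* The residual SD is the SD of change × √((1 + r)/2), where r is the correlation between baseline and follow-up. No r is given, so a range is assumed.

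| r (assumed) | Residual SD | Power at 25 per arm |
|---|---|---|
| 0.3 | 27.0% | 73% |
| 0.5 | 29.0% | 67% |
| 0.7 | 30.9% | 61% |
| 0.9 | 32.6% | 56% |

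Every value is below 80%.

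*Reading B: 24 is already a two-sample, per-arm figure.*
- 24 per arm and 80% power give d = 0.826, so the implied SD is 20 / 0.826 = 24.2%.
- At 25 per arm, power is 82%.

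**COMP and CPII (n = 7).** Reading A gives d = 1.27 and an SD of change of 20 / 1.27 = 15.7%. At 25 per arm the between-arm noncentrality is 1.27 × √12.5 = 4.5, and power is about 99%; 11 per arm would be enough for 80%. Reading B implies a larger d (1.63), so power is higher still.

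**The case against.** The strongest reply is that the section never says paired, one-group or within-group. The reference to baseline could be only the scale on which an arm difference is expressed, and the move to 25 for each group, in a paragraph that ends on a parallel design, fits a two-sample calculation. No SD is printed that would decide between the readings, and both fit n = 24. This stands. A reader might infer that the trial is shown to be underpowered, at 54%. The document does not support that: the 54% holds only if the calculation was paired.

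A reader might also extend the shortfall to every primary marker, because the n = 7 sentence has the same wording. That is not supported either, since COMP and CPII have about 99% power even on the paired reading.

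Two further points have some force. The 54% is for an unadjusted comparison of change, and adjustment for the baseline value would raise it. The Statistical analysis section does not list the baseline marker among its covariates, however, and power stays below 80% over the assumed range of correlations. The covariates that it does list (BMI, age, physical activity, vitamin D) could also change precision by an amount that cannot be calculated here.

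Last, a journal article may leave the SD and its source to the full protocol, so their absence alone is no fault. The point does not rest on it. The article makes a specific power claim for one quantity and uses it to set the arm size for another.

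**Conclusion.** The point holds in conditional form, for CTX-II/creatinine and CTX-II/CPII. As printed, the paragraph does not establish 80% power for GSM versus placebo on these ratios, and neither reading leaves it correct. On the paired reading, the n is wrong for the contrast: power is about 54% at 25 per arm (about 56-73% with baseline adjustment), and 80% power is reached only for a difference of about 27%. On the two-sample reading, power is about 82% and the effect is misdescribed. The literal wording favours the first reading but does not prove it.

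For COMP and CPII only the wording needs correcting. All the figures rest on a two-sided 0.05 level, back-solved SDs and no mean change on placebo; the adjusted range also rests on assumed correlations.

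**What to change.** Restate the Sample size paragraph for the between-arm difference in change at week 12, and print the SD used and its source. Then take the branch that matches the calculation actually done:

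- If it was paired, state for the CTX-II ratios the between-arm power and detectable difference that 25 per arm delivers. With an SD of change of 33.5%, these are about 54% for a 20% difference and about 27% detectable with 80% power. If the analysis will adjust for the baseline marker, say so and give the correlation assumed.
- If it was two-sample, describe the 20% as a difference between groups instead of a difference relative to baseline.

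Correct the n = 7 sentence in the same way; its power conclusion does not change. No participants need to be added, and the Trial status section says recruitment is already complete. The cost is one reworded paragraph, and the stated power for the CTX-II ratios may become less favourable.

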### Study population

Fifty apparently healthy postmenopausal women aged 55 to 75 years will be recruited by advertisement on campus and by using a recruitment agency, Trial Facts (https://trialfacts.com/).

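### The planned sample is given as both 50 and 55; if 50 are randomised, the plan's own 10% dropout leaves fewer than the 24 per arm it requires

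*Protocol article*

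**What the plan says.** All statements are in the protocol article.

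- **Sample size, requirement.** For CTX-II/creatinine and CTX-II/CPII, "a sample size of 24 is required to detect a 20% relative difference from baseline with 80% power".
- **Sample size, next sentence.** "Hence, 25 subjects will be recruited for each group (GSM and placebo"), which is 50 in total.
- **Sample size, last sentence.** The trial is to "recruit 55 (allowing for 10% potential dropout rate"), giving 27–28 per arm.
- **Abstract, Method.** The text opens "Fifty overweight or obese" and continues "postmenopausal women (aged 55–75 years) will be recruited by advertisement".
- **Study population.** "Fifty apparently healthy postmenopausal women aged 55 to 75 years will be recruited".
- **Enrollment and washout period, randomization.** After washout, participants are allocated to GSM (n = 25) and placebo (n = 25) and followed for 12 weeks.

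The Trial status section reports that recruitment is complete, under protocol version 3.0 of 27 May 2021. It does not give the number randomised.

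**The concern.** One design figure has two values, and they conflict within the Sample size section as well as across sections. The same verb, recruit, is attached to 25 per group and to 55. The randomisation section then attaches 25 and 25 to allocation, which comes before any loss to follow-up.

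The two values differ in consequence. Only 55 makes room for the dropout that the plan itself expects. An allocation of 25 per arm leaves a margin of one participant above the stated requirement. A reader of the eventual report also cannot judge recruitment against plan: 50 randomised would look like a shortfall against the Sample size section, and 55 would look like over-recruitment against the abstract, Study population and randomisation sections.

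**Working it through.** **Inputs from the article.** Required number 24; power 80%; dropout 10%; totals of 50 (25 + 25) and 55 (27–28 per arm); 1:1 allocation (abstract); significance level 0.05 (Statistical analysis).

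**Assumptions.** (a) The 24 is per arm. The article does not say so directly, but it moves from 24 straight to 25 for each group. (b) The test is two-sided; sidedness is not stated. (c) No SD or coefficient of variation is given, so the 24 itself cannot be reproduced and is taken as it stands.

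**Step 1. Reproduce 55.**
- Adding 10% to 50: 50 × 1.10 = 55, or 27.5 per arm, which matches 27–28.
- Dividing by the retention rate, from the required 24: 24 / (1 − 0.10) = 26.7, so 27 per arm and 54 in total.

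The figure of 55 reproduces by the first route and exceeds the minimum from the second.

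**Step 2. Expected completers = N × (1 − 0.10).**

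| Randomised | Completers | Per arm | Against 24 |
|---|---|---|---|
| 50 | 45.0 | 22.5 | below |
| 54 | 48.6 | 24.3 | met |
| 55 | 49.5 | 24.75 | met |

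With 55 split 27 and 28, even the smaller arm keeps 27 × 0.9 = 24.3 in expectation. With 25 per arm, the requirement survives only if no more than 25 − 24 = 1 participant is lost in that arm, a loss of 1/25 = 4%.

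**Step 3. Scale of the power loss.** Solve for the standardised difference d that gives 80% power at n = 24, then recompute power at other n.

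| Calculation | d | n = 22 | n = 22.5 | n = 23 | n = 24.75 |
|---|---|---|---|---|---|
| Two-sample t | 0.826 | 76.3% | 77.3% | 78.2% | 81.3% |
| Paired t | 0.597 | 76.2% | 77.2% | 78.2% | 81.3% |
| Two-sample, normal approximation | 0.809 | 76.5% | 77.4% | 78.3% | 81.2% |

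All three give about 76–78% at 22–23 per arm and about 81% at 24.75 per arm. The paired row is included because the requirement is worded as a change from baseline; the result does not depend on which reading is taken.

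**The case against.** The strongest defence is that 55 is the recruitment target and 50 the number expected to complete, with the other sections loosely worded. This is plausible. The Sample size section ends on 55, names the dropout allowance, and 55 × 0.9 = 49.5 is close to 50. But no section calls 50 the completers. Three attach it to recruitment and the fourth to allocation. The defence would reduce the defect to wrong labels; it would not remove it. The flowchart is not available to settle the matter.

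The power figures are also open to objection. They require that 50 were randomised, that the full 10% was lost, that 24 is per arm, and that the test is two-sided. The effect sizes are back-solved. The requirement concerns a difference from baseline, whereas the Statistical analysis section plans an adjusted two-group repeated-measures ANOVA. So 77% is not the power of the planned analysis. All of this stands, and the figure is used only to show that the shortfall is small.

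Two stronger readings are tempting and not supported:

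- **That the trial in fact runs on 50 and omits its dropout allowance.** The article does not say which number governs, and it does not give the number randomised.
- **That 55 is itself one short, because 25 / 0.9 = 27.8 would give 28 per arm and 56 in total.** That protects 25 completers per arm, but the stated requirement is 24, for which 27 per arm (54) is enough.

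**Conclusion.** The inconsistency is in the current text and should be corrected. At least one statement of the planned sample size is wrong as written. If 50 is the number randomised, the plan's own dropout rate leaves 22–23 per arm against 24 required, and power falls from 80% to roughly 76–78%, about 2 to 4 points. If 55 is the target, about 24.75 per arm remain in expectation and the requirement is met.

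The conflict between the numbers, and the count of completers given the per-arm reading, rest on the article alone. The power figures rest further on the 24 being correct and on a two-sided 0.05 level. The main harm is that the target cannot be read from the document; the possible loss of power is modest.

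**What to change.** State one planned recruitment and randomisation target, identically, in the abstract, Sample size, Study population and randomisation sections.

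- **If the dropout allowance is meant:** give 55 (27–28 per arm) in all four places. Keep 24 per arm as the requirement, and label 50 explicitly as expected completers if that is what it is.
- **If the target was really 50:** delete the dropout-allowance statement. Say that 80% power holds only with no more than one loss per arm, and that it would be about 77% after 10% dropout, with the assumptions behind that figure.

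In either case, report the number actually randomised per arm separately, under Trial status. It should not overwrite the planned target, because that would hide whether the target was met.

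The cost is a text correction. Recruitment is complete, so nothing changes in conduct. Under the second option the article would acknowledge slightly lower power.

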### Study population

Fifty apparently healthy postmenopausal women aged 55 to 75 years will be recruited by advertisement on campus and by using a recruitment agency, Trial Facts (https://trialfacts.com/).

### Informed consent form procedure

Written informed consent will be obtained from participants before commencing data collection. The researcher provides an explanation on details of the trial, including the purpose, follow-up processes, sample collections, and other related procedures. After the eligible participant agrees to undergo the explained procedure, the research team will give the consent form to the participant to read. The participants are allowed to ask any questions regarding the consent form and trial involvement. If the participant voluntarily agrees to participate, the participant will sign the consent form. If the participant requires additional time to make more informed and voluntary decisions, the researcher will wait and allow this opportunity. Only the main researcher will be involved in obtaining the written informed consent. A copy of informed consent will be attached in the file with the study ID. The consent form is provided in Supplementary File. Currently, further analyses are not planned. Nevertheless, any future additional analysis will require institutional and ethics committee approval.

